### Home exercises

Home exercises consist of quadriceps and hip muscle retraining and stretching. The exercises are performed each day in accordance with the regime proposed by McConnell [12].

### Compliance

Compliance with the supervised intervention is recorded as the number of times each student participates in the group training. Good compliance is defined as participation in at least 80% of the supervised group training sessions. Poor compliance is defined as participation in less than 40% of the group training sessions. Compliance in home exercises will be monitored by weekly follow-up using Short Message System (SMS). Good compliance in home training is defined as self-reported participation in at least 70% and poor compliance is defined as below 40%.

### Adherence to treatment

To increase adherence to the designated intervention and to optimise retention, parents are invited to participate in all aspects of the study. Communication with the students is done by telephone or email. The day before appointments, students are sent a reminder by SMS. If students know in advance that they cannot participate in the group training sessions, they are asked to send an SMS to the physiotherapist that states they will not be participating.

If students do not show up for training twice in a row, and do not cancel through SMS they are telephoned by the physiotherapist who asks them in a friendly manner when they will return. If the students do not answer the phone twice or do not call back, they receive an SMS that tells them that they will be contacted the next day. If they fail to reply to the SMS or do not answer the phone the following day, they are sent a letter requesting contact.

### Co-interventions

Students with PFPS are asked to refrain from all other co-interventions during the intervention period starting 72 hours before participation in the study. Pre-existing foot orthoses are allowed, but patients are not allowed to change orthoses or modify their current orthoses during the study period. Current or prior analgaesic use for the current knee pain is registered during baseline testing and all follow-ups.

### Observational cohort

Those who do not wish to participate in the randomisation procedure are followed as an observational cohort. The observational cohort is followed at the same time-points and is asked which treatment they have received.

### Outcome measurements

#### Self-reported outcome measurements

Self-reported questionnaires are filled out by the students with PFPS at baseline, 3, 6, 12 and 24 months after inclusion in the study. A physiotherapist not involved in the treatment, will hand out all questionnaires during follow-up and answer questions from the students. The primary outcome measure is perception of recovery after 12 months measured on a 7-point Likert scale ranging from "completely recovered" to "worse than ever". Students are categorised as "recovered" if they rate themselves as **"**fully recovered**" **or **"**strongly recovered**"**. Students rating themselves in one of the other five categories from **"**slightly recovered**" **to **"**worse than ever" are categorised as "not recovered" [11]. Secondary outcomes include Knee Injury and Osteoarthritis Outcome Score (KOOS) [22]. The change from baseline to each point of follow-up in the average score of the five KOOS subscale scores (KOOS_5_) covering pain, symptoms, activities of daily living, difficulty in sports and recreational activities, and quality of life are used. Further, EQ5D is used as s self-reported generic measure of health status [23].

#### Objective outcomes

A subgroup of 15 female students with PFPS from each cluster (a total of 60 students) is invited to participate in a sub-study investigating the effect of interventions on changes in neuromuscular function and isometric strength of the quadriceps. A person not involved in the treatment or diagnostics of the students randomly calls newly diagnosed subjects and asks them to participate. The students will undergo quadriceps strength measurements and two tests of neuromuscular function of m. vastus medialis and m. vastus lateralis before treatment and again after three months of treatment. Surface Electromyography (sEMG) is collected during two different conditions: stair walking and semi-squat at 90 degrees flexion at the knee joint. These measurements are carried out with the assessor blinded and before students are randomised. At three months follow-up, the same assessor tests all 60 students again. Before students are tested at three months follow-up, they are told not to reveal which intervention group they were assigned to. The assessor does not participate in any other parts of the study.

Bipolar surface electrodes (Ambu A/S, Neuroline, Ballerup, Denmark) are placed on the muscle bellies of m. vastus medialis (VM) and lateralis (VL) with an interelectrode distance of 22 mm. The electrode for VM is placed over the muscle belly 4 cm superior to and 3 cm medial to the superomedial patella border and orientated 55° to the vertical. The electrode for VL is placed 10 cm superior to and 6-8 cm lateral to the superior border of the patella and orientated 15° to the vertical [24]. The ground electrode is placed over the tibial tubercle.

#### Isometric strength measurement

The testing set up includes a portable handheld dynamometer (HHD) and an examination table. Muscle strength is tested with the Power track II commander (JTECH Medical, Salt Lake City, Utah, USA). A physiotherapist with previous experience using the HHD performs all measurements. Only isometric extension strength of the knee is tested.

The test position is chosen based on procedures that are often applied in clinical settings and have proven reliable[25]. The students are told to stabilise themselves by holding onto both sides of the table with their hands. Using a secure strap tied to the examination table the dynamometer is secured to the table and the patient exerts a 5-sec. isometric maximum voluntary contraction (MVC) against the dynamometer. Students are asked to perform one isometric sub-maximal contraction, to ensure that the correct action is performed. After a 30-sec. rest period the individual test is performed four times. The highest value of four consecutive measurements and the mean of the three highest values are used as the outcome. Students are given a 30-sec. rest period between each trial. The standardised command by the examiner is ''go ahead-push-push-push-push and relax''.

### Semi squat

After isometric strength measurement, sEMG is recorded during an isometric holding test. The holding test consists of a semi-squat. Students are asked to position themselves with a 90-degree knee angle, and to keep as steady as possible. They perform one practice trial of 5 sec. After the practice trial they have 2 minutes of rest. Afterwards they are asked to resume the position and when the knees are in a 90-degree angle, the sEMG recordings of VM and VL and signal from the knee goniometer start. A total of 20 consecutive seconds is recorded. The sEMG-signal from VM and VL are analysed with respect to quantifying the nonlinear complexity of the sEMG signal as a composite measure of neuromuscular control [26].

### Stair walking

Students walk up and down a stairway with 10 consecutive steps. They walk up and down once corresponding to 10 steps ascending and 10 steps descending. An electronic knee goniometer is used to record the flexion/extension movement at the knee. The knee goniometer consists of a potentiometer attached to two thermoplastic cups that secure around the tibia and femur. sEMG from VM and VL and kinematics are recorded from the most painful knee.

### Sample size

From the study done by Moelgaard et al [4], we expect that at least 6% of the students will be diagnosed with PFPS. This corresponds to at least 150 students with PFPS among the 2500 students.

Based on the study done by van Linschoten et al [11] and Clark et al [27] we expect a 30% difference between intervention groups in the two categories "recovered" and "not recovered". We expect a 20% recovery in the patient education group, and 50% recovery in the group receiving patient education combined with multimodal physiotherapy. Sample size calculations show that at least 51 subjects in each group are needed to detect a statistical difference (power 0.90, alpha 0.05). To account for a drop-out rate of 10%, a minimum of 56 patients is included in each group.

The sample-size of 60 students (2 × 30 students) in the sub-study is based on the complexity of the sEMG-signal from VM during semi-squatting. Based on pilot data, 25 students are needed in each group to detect a 15% difference (0.104 vs. 0.120 Sample Entropy, standard deviation of 0.02, 80% power) between groups at three-months follow-up. To account for loss to follow-up, we increase the sample size to 2 × 30.

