### Patient selection

Four upper secondary schools were invited to participate in the study. All four schools accepted the invitation. All students (approximately 2500), aged 15-19 years, in the schools are invited to answer an online questionnaire as part of their physical education lessons. The students who report knee pain are contacted by telephone and offered a clinical examination by an experienced rheumatologist who evaluates which students are eligible to enter the study (Figure 1).

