### Randomisation

Subjects who fit the inclusion criteria are offered to participate in the study. After all subjects have undergone a clinical examination and signed an informed consent, students are cluster-randomised into two intervention groups based on which school they attend. Cluster randomisation is chosen to minimise the bias that could be introduced if more than one student in each class is diagnosed with PFPS, but randomised to different treatment groups.

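### The stated 90% power with 51 students per group is calculated for individually randomised students, but the trial randomises four schools, two per arm

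*Protocol article*

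**What the plan says.** The Patient selection section fixes the number of clusters: "Four upper secondary schools were invited to participate in the study. All four schools accepted the invitation". The Randomisation section makes the school the unit: "students are cluster-randomised into two intervention groups based on which school they attend". The two intervention sections (education alone; education plus multimodal physiotherapy) each refer to two clusters, so the split is two schools against two.

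The Sample size section gives the planning rates, "We expect a 20% recovery in the patient education group, and 50% recovery in the group receiving patient education combined with multimodal physiotherapy", and then the result: "Sample size calculations show that at least 51 subjects in each group are needed to detect a statistical difference (power 0.90, alpha 0.05". The only inflation after that is for loss: "To account for a drop-out rate of 10%, a minimum of 56 patients is included in each group". The section names no ICC, design effect, cluster size or number of schools. The same section sizes the electromyography sub-study for 80% power: "25 students are needed in each group to detect a 15% difference", raised to 30 per group for loss to follow-up.

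**The concern.** Students at one school may resemble each other in outcome more than students at different schools. In the physiotherapy arm each school also has its own physiotherapist, so therapist and school effects cannot be separated there. Any such similarity reduces the information per student, and with only two schools per arm it also limits how much extra recruitment can recover.

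The hypothesis in the Background is confirmatory: a significantly larger proportion recovered at 12 months. If the 90% is taken at face value, a null result will be read as negative from a well-powered trial. The planned 30-point difference could in fact have been missed with a probability well above 10%.

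**Working it through.** **Inputs from the protocol article.** Recovery 20% and 50%; alpha 0.05 (sidedness not stated; two-sided reproduces the figure); power 0.90; 51 evaluable per group; 10% drop-out; at least 150 expected cases (all from Sample size). Four schools (Patient selection), two per arm (intervention sections).

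**Assumption.** The documents give no ICC. A range of 0.005 to 0.05 is used, with equal school sizes.

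**Step 1: reproduce the 51.** Pooled two-proportion formula with mean proportion 0.35:

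n = [1.960 × √(2 × 0.35 × 0.65) + 1.2816 × √(0.20 × 0.80 + 0.50 × 0.50)]² / 0.30²
= (1.3221 + 0.8206)² / 0.09 = 51.01.

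The power at n = 51 is 0.900. The unpooled version gives 48 and the continuity-corrected version 58. The printed figure is therefore the unadjusted number for independent students.

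**Step 2: power with a design effect.** With m students per school, DE = 1 + (m − 1) × ICC and effective n per arm = n / DE. Then

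power = Φ{[0.30 × √(effective n) − 1.960 × √0.455] / √0.41}.

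Two cases are shown: 51 per arm (m = 25.5), and 150 × 0.90 / 2 = 67.5 per arm (m = 33.75).

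| ICC | DE, 51 per arm | Power, 51 per arm | DE, 67.5 per arm | Power, 67.5 per arm |
|---|---|---|---|---|
| 0 | 1.00 | 90% | 1.00 | 96% |
| 0.005 | 1.12 | 86% | 1.16 | 93% |
| 0.01 | 1.25 | 83% (0.825) | 1.33 | 90% |
| 0.02 | 1.49 | 75% | 1.66 | 82% |
| 0.05 | 2.23 | 57% | 2.64 | 62% |

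**Step 3: can more students restore 90%?** With k = 2 schools per arm and 51 required under independence,

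n per arm = 51 × (1 − ICC) × 2 / (2 − 51 × ICC).

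This gives 59, 68 and 102 evaluable per arm at ICC 0.005, 0.01 and 0.02. The denominator reaches zero at ICC = 2/51 = 0.039. From there no number of students in these four schools gives 90%.

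**Step 4: conservative bound.** A school-level t test has 4 − 2 = 2 degrees of freedom and a critical value of 4.303. With noncentrality 0.30 / √(0.41 / effective n) and 51 per arm, power is about 45% at ICC 0, 39% at 0.01, 34% at 0.02 and 26% at 0.05.

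**Step 5: sub-study.** The standardised difference is (0.120 − 0.104) / 0.02 = 0.8. Then n = 2 × (1.960 + 0.8416)² / 0.8² = 24.5, or 25 per group, again the figure for independent students. With m = 12.5, DE = 1 + 11.5 × ICC and power = Φ[0.8 × √(25 / (2 × DE)) − 1.960]. This is about 76%, 72% and 62% at ICC 0.01, 0.02 and 0.05, before any penalty for degrees of freedom.

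**The case against.** The best defence has three parts.

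- **A journal article condenses.** An ICC may stand in a fuller document. This does not rescue the figure. The 51 equals the unclustered answer, so no unprinted ICC above 0 can turn it into a cluster-adjusted 90%.
- **The ICC may be small and recruitment may exceed the minimum.** This stands in part. With 67.5 evaluable per arm, design-effect power is about 93% at ICC 0.005 and 90% at 0.01. But that needs every expected case to enrol, and the protocol provides an observational cohort for those who decline randomisation.
- **The 2-degree-of-freedom test is too strict.** This also stands in part. The Statistical analysis section plans a logistic regression for repeated measurement, not a school-level t test, so those figures are a lower bound.

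A reader might infer stronger conclusions that the documents do not support:

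- That the trial's power simply is 26% to 39%. This rests on an assumed ICC and on a test that is not planned.
- That adding students within four schools can never help. Under the design-effect calculation it does help at small ICC, as step 3 shows.
- That significance is impossible because there are 6 ways to allocate two of four schools, so a two-sided permutation p-value cannot fall below 2/6 = 0.33. The arithmetic is right, but no such test is planned.
- That classes should be randomised instead. The Randomisation section does name the class when it explains the choice of clustering, but this would be a redesign with its own contamination and staffing costs. It is not needed to correct the power statement.

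**Conclusion.** The point holds. The arithmetic behind 51 is right for the formula used, but that formula belongs to individual randomisation and the trial randomises schools. At the planned 51 evaluable per arm, the power is below 90% for any ICC above 0. How far below depends on an ICC the documents do not give, and falls within the range tabulated above. Larger recruitment could bring the power back to 90% only at the low end of that range. Taking the school as the unit of analysis gives less than half the stated power at 51 per arm for every ICC from 0.01 upward, and half of it at ICC 0. The sub-study has the same fault, but it is secondary and does not carry the weight of the point.

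**What to change.** In Sample size, replace the 0.90 with the power of the four-school design. State that there are two schools per arm, the assumed ICC range, the design effect and the resulting range of power. Give it at 51 evaluable per arm and, if wished, at the recruitment now expected. Add the 2-degree-of-freedom figures as the conservative bound, and note the ICC (about 0.039) above which more students cannot restore 90%. Treat the sub-study's 80% in the same way.

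Describe the main result as an estimated difference with a confidence interval that reflects school-level randomisation, not as the outcome of a 90%-powered test.

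This changes wording only: recruitment, allocation and delivery stay as they are. The cost is a less favourable stated power.

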**Methods/Design:**

This study is a single blind pragmatic cluster randomised controlled trial. Four upper secondary schools have been invited to participate in the study (approximately 2500 students, aged 15-19 years). Students are asked to answer an online questionnaire regarding musculoskeletal pain. The students who report knee pain are contacted by telephone and offered a clinical examination by a rheumatologist. Subjects who fit the inclusion criteria and are diagnosed with PFPS are invited to participate in the study. A minimum of 102 students with PFPS are then cluster-randomised into two intervention groups based on which school they attend. Both intervention groups receive written information and education. In addition to patient education, one group receives multimodal physiotherapy consisting primarily of neuromuscular training of the muscles around the foot, knee and hip and home exercises.

The students with PFPS fill out self-reported questionnaires at baseline, 3, 6, 12 and 24 months after inclusion in the study. The primary outcome measure is perception of recovery measured on a 7-point Likert scale ranging from "completely recovered" to "worse than ever" at 12 months.

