**Figure 1 F1:**
[figure not shown]
**Flowchart**. Subjects who are diagnosed with PFPS will be invited to participate in the study. 104 students diagnosed with PFPS will be cluster randomised into two groups based on which school they attend.

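### The protocol gives three different totals for the students to be randomised (102, 104 and 112), and the two lower ones do not carry its own 10% drop-out allowance

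*Protocol article*

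**What the plan says.** Three places in the protocol article state how many students with PFPS are to be randomised.

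- Abstract, Methods/Design: "A minimum of 102 students with PFPS are then cluster-randomised into two intervention groups".
- Figure 1 legend: "104 students diagnosed with PFPS will be cluster randomised into two groups".
- Methods, Sample size: "To account for a drop-out rate of 10%, a minimum of 56 patients is included in each group". With two groups this is 112.

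The last figure is built on a calculation in the same section. The assumed recovery rates are "We expect a 20% recovery in the patient education group" and "50% recovery in the group receiving patient education combined with multimodal physiotherapy", with "power 0.90, alpha 0.05", and the result is that "at least 51 subjects in each group are needed to detect a statistical difference".

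Only the 102 and the 56 per group are called minima. The 104 is given simply as the number randomised.

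**The concern.** All three statements describe the same quantity, the number of students entering randomisation, and they differ. The Abstract's figure equals twice the 51 per group that the Sample size section requires before drop-out. A number that should be left at the end has been presented as the number at the start. The 104 is neither 2 × 51 nor 2 × 56, and its origin is not given.

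Two things are at stake. A reader cannot tell from the protocol what size the trial was planned to reach. A trial that randomised 105 students, for example, would satisfy the Abstract and miss the Sample size section. And a trial that only just met the Abstract or Figure 1 figure would have little or no room for the 10% loss that the protocol itself expects.

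**Working it through.** **Inputs** (all from Methods, Sample size): recovery 0.20 and 0.50; alpha 0.05; power 0.90; two equal groups; drop-out 10%. The section names neither the formula nor the sidedness, so two-sided testing is assumed here.

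**Step 1. Reproduce the 51.**

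- Pooled normal approximation, with mean rate (0.20 + 0.50)/2 = 0.35:
  n = [1.960 × √(2 × 0.35 × 0.65) + 1.282 × √(0.20 × 0.80 + 0.50 × 0.50)]² / 0.30² = 51.01 per group. This is 51 to the nearest integer and 52 if always rounded up.
- Arcsine formula: 50.7, rounded up to 51.

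The stated 51 therefore reproduces. Other variants fit less well: the unpooled formula gives 48, the continuity-corrected one 58 and the one-sided one 42.

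**Step 2. Reproduce the 56.**

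- 51 × 1.10 = 56.1, which rounds to the stated 56.
- To have 51 left after 10% loss: 51 / (1 − 0.10) = 56.67, rounded up to 57.
- Check: 56 × 0.90 = 50.4; 57 × 0.90 = 51.3.

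The stated 56 is one student per group short of what would retain 51.

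**Step 3. Compare the three totals.**

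- 2 × 51 = 102, the Abstract's figure, with no allowance for loss.
- 104 / 2 = 52 per group, which matches no group size in the section.
- 2 × 56 = 112, the Sample size figure.

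**Step 4. Apply the protocol's 10% loss to each total.** Power comes from the same pooled formula solved for power, Φ[(0.30 × √n − 1.960 × √0.455) / √0.41], where n is the evaluable number per group, 0.455 = 2 × 0.35 × 0.65 and 0.41 = 0.16 + 0.25.

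| Randomised | Evaluable per group | Power |
|---|---|---|
| 102 (Abstract) | 51 × 0.90 = 45.9 | 86.6% |
| 104 (Figure 1 legend) | 52 × 0.90 = 46.8 | 87.3% |
| 112 (Sample size) | 56 × 0.90 = 50.4 | 89.6% |
| 114 (57 per group) | 57 × 0.90 = 51.3 | 90.2% |

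At n = 51 per group the same formula gives 90.0%, the stated target.

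**The case against.** The strongest reply is that the conflict may never affect the trial. All of the roughly 2500 students at the four schools are invited, allocation comes only after everyone has been examined and has consented, and at least 150 diagnosed cases are expected. Recruitment is a single sweep of four schools. A reader might infer that 102 or 104 is a point at which recruitment may stop, but no section says so. The 87% scenario arises only if eligibility or consent turns out low. This stands, and it limits the consequence. It does not remove the contradiction, and a low yield is possible because students may decline randomisation and join the observational cohort: 102 is 68% of 150 (102/150) and 112 is 75% (112/150).

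A reader might also infer that 56 instead of 57 is a material sample-size error. It is not. The shortfall is 0.6 of a student per group (51 − 50.4) and about 0.4 points of power (90.0% − 89.6%), under a formula that the protocol does not name.

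Finally, a reader might argue that allocation by school makes a per-group minimum impossible to guarantee, so that only a total should be stated. The document does not support that contrast. School counts are known before allocation, so the arm sizes under any pairing of schools can be checked. The total is not guaranteed either, since it depends on prevalence, eligibility and consent in four fixed schools.

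**Conclusion.** The inconsistency is real: 102, 104 and 112 are unreconciled figures for one quantity, so at least two of the three places are wrong as written. The Abstract's 102 is the number before the drop-out allowance, and the 104 cannot be derived from anything stated.

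If the trial randomised only 102 or 104 and lost 10%, power would be about 87%, some 3 points below the stated 90%. The power figures assume a two-sided pooled formula, equal groups and independent students. Allocation by school is not allowed for in any of them, and positive correlation within schools would lower them all. The difference between 56 and 57 per group is a secondary rounding correction, to be made while the total is being settled.

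**What to change.** State one randomised total in the Abstract, the Figure 1 legend and the Sample size section. Either option is workable:

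- **112 (56 per group)**, adding that 10% loss leaves about 50 evaluable per group and about 89.6% power under independence; or
- **114 (57 per group)**, from 51/0.90 rounded up, if 51 evaluable per group is the aim.

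If 102 is kept anywhere, label it as the evaluable number before the drop-out allowance, not as the number randomised.

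The cost is a text correction in three places. Choosing 114 over 112 raises the planned minimum by two students, against at least 150 expected cases.
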